## Abstract

**Introduction**: Globally, there is an epidemic of opioid use disorders. Locally, in Singapore, there is an increase in the number of individuals abusing opioids. The advances in experimental psychology have highlighted the need to modify unconscious, automatic biases. These automatic, unconscious biases result in individuals having preferential attention to substance-related cues in their natural environment, thus leading to a slip or relapse back into their underlying addictive disorders. Prior studies have demonstrated not only the presence of robust attentional biases amongst individuals with opioid use disorder, even when maintained on methadone; and the effectiveness of bias modification amongst these individuals. There remains limited evaluation of attention bias modification amongst a treatment-seeking cohort of Asian individuals. The objective of this pilot is to ensure that the methods of the planned definitive randomized trial could be conducted. **Methods and Analysis**: A non-blinded pilot randomized trial will be conducted. A total of 30 participants will be randomized to receive either the conventional application or the newly designed co-designed application. In order to identify these 30 participants, 60 participants will be recruited and screened to determine if they have baseline biases. Participants will be recruited from the inpatient unit at the National Addictions Management Service (NAMS) Singapore. All participants who are enrolled into the trial will complete a baseline assessment task, and a bias modification assessment and modification task daily. They will have to complete a baseline demographic and clinical information questionnaire, as well as a cravings rating scale before and after the intervention daily. Perspectives—that of self-reported experiences—will be sought from the participants following their completion of three intervention tasks. Descriptive statistical analyses will be performed, and chi-square and ANOVA analyses will be performed. Qualitative analyses will be undertaken for the perspectives shared. **Ethics and Dissemination**: Ethical approval has been obtained from the National Healthcare Group’s Domain Specific Research Board (DSRB) (approval number that of 2019/00934). The findings arising from this study will be disseminated by means of conferences and publications.

## 1. Introduction

Substance use disorders are becoming increasingly prevalent. In 2015, the United Nations Office of Drugs and Crime (UNDOC) estimated that at least a quarter of a billion individuals have experimented with substances, and 0.06% of the global adult population (or 29.5 million individuals) were diagnosed with a substance use disorder [1]. According to the latest report released by the UNDOC, there has been an increase since then, with an estimated 35 million individuals diagnosed with substance use disorder [1]. The UNDOC’s latest report also highlights there being a treatment gap, given that only one in every seven individuals have received treatment. In 2015, the most common substances that were abused were that of cannabis, opioids and amphetamines, with annual prevalences of these of 3.8%, 0.7% and 0.77% respectively, each year [1]. In 2019, there has been a large increase in the number of opioid-using individuals; in fact, a 56% increment from previous estimates [1]. It is well-known that substance use disorders are associated with significant morbidities and mortality. With regards to mortality, two thirds of individuals diagnosed with substance use disorders who died in 2017 were opioid users [1]. With regards to morbidities, an estimated 1.4 million substance-using individuals are diagnosed with HIV (human immunodeficiency virus), and another 5.6 million individuals with hepatitis C [1].

Globally, there is an epidemic of opioid use, according to the World Health Organization. In 2016, an estimated 27 million individuals were diagnosed with opioid use disorders. Most of these individuals have abused illicit opioids, but an increasing number are using prescription opioids, such as tramadol and oxycodone [2]. Several factors are responsible for the current epidemic of abuse of prescription opioids, and they include that of the increased accessibility to prescription opioid analgesics, the enhanced purity of heroin and the introduction of more potent illicit fentanyl compounds [3,4]. Several public health approaches have been considered, such as that of prescribing only the right quantities, heightened measures to prevent diversion and changes in drug formulation in order to prevent abuse [3,4]. Whilst these approaches are essential, there needs also to be efficacious treatment for opioid use disorder. Opioid substitution medications like methadone (opioid receptor agonist) and that of buprenorphine (partial opioid receptor agonist) are routinely used. Psychosocial treatment is also routinely coupled with pharmacological treatment, to help in harm minimization and eventual abstinence. 

In Singapore, there remains no recent large-scale epidemiological study that has been conducted for substance use disorders. However, in 2004, the World Health Organisation estimated the prevalence of substance use disorders in females to be 0.07% and in males to be 1.40% [5]. Statistics from the Central Narcotics Bureau Singapore (2018) have revealed that heroin was among the top three most commonly abused drugs apart from that of methamphetamine and novel psychoactive substances (NPS) [6]. Traditionally pharmacological medications, that of opioid substitutes, have been recommended in conjunction with psychosocial interventions. However, in Singapore, opioid substitutes are not available, due to Singapore’s zero tolerance for drug use policy. Instead, individuals with opioid use disorders undergo detoxification using symptomatic medications, followed by psychological interventions [7]. 

In the Singapore context, psychosocial interventions are of particular importance, given the limited pharmacological options that are available. Psychological therapies help individuals to achieve and maintain abstinence. Traditionally, therapies like cognitive behavioural therapy for relapse prevention, mindfulness-based relapse prevention and cue-exposure therapies are used. Whilst these therapies, such as cognitive behavioural therapy, have been proven to be effective for disorders including alcohol disorders, in some studies, a proportion of individuals still relapse following intervention [8]. It is likely that these therapies have addressed only the cognitive control processes leading someone to lapse or relapse into an addictive disorder, but not the underlying unconscious processes [9]. The advances in experimental psychology have led to the greater understanding of these unconscious, automatic biases—that of attention and approach biases [9,10]. The dual-process theoretical approach states that attention biases (preferential allocation of attention to substance-related cues) and approach biases (automatic action tendencies to reach out for substance-relate cues) develop as the repetitive usage of a substance leads to increased automatic processing and automatic tendencies to acquire the substance, with the inhibition of the normal cognitive control processes [10,11]. Maclean et al. (2018) [12], in their prior review, highlighted there being robust attentional biases present amongst individuals with opioid use disorders. This was based on the evidence synthesized from 21 studies. Maclean et al. (2018) [12] also reported there being a moderate to large effect size for the presence of attentional biases amongst individuals with opioid use disorders, as compared to healthy controls. With regard to attention bias modification, studies like that of Hietmann, J. et al. (2018) [13] in their systematic review, which included nine studies on alcohol use disorder, six studies on nicotine use and three on opiate use disorders, reported that whilst there have been negative findings, multi-session attention bias modification has had positive effects on attentional change, particularly for alcohol use disorders. Ziaee et al. (2016) [14] reported bias modification to be effective in reducing attention bias for drug-related stimuli and temptations to use, amongst individuals maintained on methadone maintenance therapy. However, the fact that attentional biases are still persistent despite being on methadone maintenance therapy also highlights the need for specific intervention to address these unconscious attentional processes [15]. Most of these studies are limited to the evaluation of attentional biases in western individuals, and to date, from our knowledge, there remains only a single study (Zhang et al., 2019) [15] that has explored attentional bias modification in an Asian cohort of substance-using individuals. In Zhang et al. (2019)’s [15] prior study, they reported the feasibility and acceptability of a mobile attention bias intervention and reported there being individuals without baseline biases. In their sample of 30 participants, 17 participants had a diagnosis of opioid dependence, of which eight had an absence of baseline biases [16]. Zhang et al. (2019)’s [15] prior study did demonstrate that there was a change amongst participants with baseline biases, and this warrants further exploration. 

Zhang et al. (2019) [17] subsequently undertook a co-design study and involved both healthcare professionals and patients in the joint conceptualization of a new intervention to address the shortcomings of the conventional application, particularly that of motivation to continue training and the inherent repetitiveness of the task. Both groups of participants suggested for there to be a lengthier stimulus presentation interval at the start of the intervention, before gradual decreasing to a short presentation interval. Gamification strategies, mainly that of feedback, were recommended. To date, Zhang et al. (2019) [17] remains the first study to have involved participants in the design of an attention bias modification intervention, and there needs to be further evaluation of the co-design application against that of the original application to determine if it is more effective. 

The objective of the current pilot randomized trial is to determine if the intended processes of the definitive study (i.e., the recruitment of participants with opioid use disorder, the process of randomization into two separate intervention arms, and the administration of the intervention) would work. The current pilot differs from the actual definitive randomized trial, in that the intent is essentially in testing out the process for the definitive trial. This pilot is of importance, as it will help identify and eliminate problems that might affect the eventual success of the definitive trial. Prior research has highlighted how as much as 85% of research investment has been wasted due to the poor design and conduct of trials [18]. Some of the previously identified issues that render a trial to be poor include a lack of systematic literature review and inadequate concealment of treatment allocation [18].

## 2. Methods

### 2.1. Study Design and Setting

The study design will be that of a non-blinded randomised controlled trial. Participants will be allocated to receiving either the conventional attention bias modification task, or that of the co-designed task. Simple randomisation will be used. The study will be conducted on the inpatient unit at the National Addictions Management Service, Institute of Mental Health, Singapore. This is a non-blinded randomised trial, as participants who are allocated to both the groups will knowingly be aware of their treatment allocation. It is also not practical for study team members to be blinded, as they are to be responsible for the group allocation, intervention and data collation. 

### 2.2. Inclusion and Exclusion Criteria

Participants are considered eligible for the study if they fulfil the following inclusion criteria, (a) aged between 21 and 65 years old; (b) primary psychiatric diagnosis of opioid use disorder; (c) for patients diagnosed with polysubstance use disorder, their primary substance of abuse needs to be that of opioids; (d) able to read and write in English; and (e) completed their detoxification program. For participation in the trial, participants are required to have baseline attentional biases (i.e., have a positive attentional bias).

### 2.3. Sampling and Recruitment

Convenience sampling will be used in the recruitment of participants over a period of 12 months, at the inpatient unit of the National Addictions Management Service (NAMS), Institute of Mental Health Singapore. The inpatient unit at NAMS offers a 2-week program, in which the first week of the program is focused on the provision of medication-assisted detoxification and the second week of the program is focused on rehabilitation. The unit can have a total of 22 inpatients at any one time. It is also crucial to note that the program is voluntary in nature, which implies that participants are free to leave the ward if they wish to, at any juncture of their inpatient treatment. All participants who have demonstrated interest in the study will be asked to undertake a baseline attention bias assessment task. Only participants who have baseline biases will be recruited into the trial and will be randomly assigned to any of the two groups by means of simple randomisation. Figure 1 provides an overview of the participant flowchart following screening and recruitment.

### 2.4. Sample Size

For the purposes of this pilot, we plan to screen 60 participants for baseline biases. Based on our prior feasibility and acceptability study [15], approximately 50% of these participants will have baseline biases. We anticipate that 50% of the participants (or 30 participants) may not have baseline attentional biases and hence would not be eligible for the eventual pilot. Therefore, the sample size for the eventual pilot is that of 30 participants, with 15 participants being randomised to receiving the co-design application and the remaining 15 being randomised to receiving the conventional applications. The sample size of 30 participants in total, with 15 in each group, was selected, taking into consideration previous pilot randomized trials evaluating web-based cognitive bias interventions for individuals with obsessive-compulsive disorder [19,20]. In those previous studies, the sample size per group ranged from between 6 and 37 participants. Moreover, based on Bell LM et al. (2018)’s [21] guidance for using pilot studies in informing the design of confirmatory studies, the proposed sample size for the pilot study if the effect size is small (i.e., Cohen D is between 0.1 and 0.3), is an estimated 25 participants per arm of the intervention. We have not performed a power computation for the purposes of the pilot, as the pilot study is supposed to inform the definitive sample size for the confirmatory trial [22,23]. 

### 2.5. Randomisation

Simple randomisation, by means of a computer program, will be used, and each participants’ treatment will be determined independently, without any constraints. In this study, the method proposed by SD Simon (1999) [24] will be used. Making use of Microsoft Excel, a spreadsheet will be created, with a column indicating the participant number of 60 participants. Another column will be created in which the intended treatment will be arranged systematically. Using a column of random numbers, by using the RAND () functionality, the column comprising of the random numbers will be sorted, which will in turn result in the treatment conditions being allocated to participants in a random and unpredictable order [25]. 

## 3. Experimental Procedure and Data Collation

**a.** 
**Screening for Eligibility**

Informed consent will be acquired from participants on the last day of their detoxification stay (Day 7), for the purposes of screening, in the presence of an impartial witness. For the screening for the presence of baseline attentional biases, participants are required to undertake an attention bias task on a tablet device. In the assessment task, participants will be shown a fixation cross for 500 milliseconds, followed by a set of images (one related to their substance of use and another neutral image that is similar in complexity). While 50% of these images will be presented for a short stimulus duration of 200 milliseconds, the other 50% of the set of images will be presented for a long stimulus duration of 2000 milliseconds. Following the disappearance of the images, participants are presented with a probe (in the form of an asterisk) for 200 milliseconds. Participants are required to indicate their response, by means of tapping the buttons on the screen, to indicate if the asterisk is presented on the left or right side. If they do not respond, they will be presented with the next trial. In the screening phase, 50% of the trials (100 trials) will involve the presentation of the probe with the substance image, and 50% of the remaining trials will involve the presentation of the probe with the neutral image. The presence of attentional bias will be computed by means of subtracting the reaction time that participants take to respond to probes that replace the neutral image from the reaction time to the probe that replaced the substance image. 

**b.** 

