**Experimental Procedure**

Participants who are screened positive (i.e., having a positive baseline biases) will be eligible to be recruited into the pilot randomized trial. Informed consent from these participants will have already been obtained in the screening stage. Participants who are ineligible (those without baseline biases) will be dismissed from the study, given due compensation and allowed to go on with their rehabilitation program. Members of the study team will orientate the participants on the use of the mobile application. Participants will be provided with a tablet device to use the mobile application daily. Participants will be also provided with a unique username and password to allow them to have access to the application daily. Participants will be required to complete the following baseline questionnaires, the baseline demographic and clinical information questionnaire, on Day 8 of their stay in the ward, or the first day of their intervention. The following baseline demographic and clinical information will be collected from the participants—that of nationality, gender, marital status, race, religion, highest level of education, housing conditions, current substance use, method of consumption of substance, quantity of substance consumed each time, frequency of use, previous treatment history, chronic diseases (psychiatric and physical disorders) and current psychiatric medications. Participants will also be required to complete a visual analogue scale for the assessment of cravings before and after undertaking the intervention. The experimental procedure will not differ for participants who are randomized to receiving the co-designed application versus that of the conventional application. Participants will be asked to spend 10 min to complete 200 repeats of the intervention task. Upon completion of the first intervention task, participants can rest for 10 min, before spending another 10 min to complete 200 repeats of the assessment task. Participants will continue to retake the intervention daily, each day they are an inpatient, except for weekends and public holidays. On the subsequent days, participants are to take the intervention task, rest for 10 min, before completing an assessment task. Participants will be asked to retake the craving questionnaire prior to and after the tasks on each of the days that they are involved in the study. Participants will be also asked to complete a questionnaire to acquire their feedback pertaining to the intervention (after they have completed three interventions). If participants request premature discharge from the ward, they are not required to return to the ward to complete the intervention. 

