**Details of Intervention Tools**

For the conventional mobile attention bias modification application, there are two tasks that participants are to undertake daily—that of the assessment task and that of the intervention task. In the assessment task, participants are presented with a fixation cross at the centre of the screen for 500 milliseconds. The fixation cross will then disappear, and a set of images will be presented. 50% of the set of images (i.e., 100 sets of images) will be presented for 200 milliseconds, and 50% of the set of the images (i.e., 100 sets of images) will be presented for 2000 milliseconds. The set of images will comprise a substance image and a neutral image, that is similar in colour, size and complexity. The images that will be used will be obtained from the Central Narcotics Bureau’s database. Following the disappearance of the images, a probe (asterisk) will appear, either replacing the substance image or the neutral image, for 200 milliseconds, before disappearing. Participants are supposed to indicate the position of the probe by selecting the buttons on the screen (i.e., left button if the probe is on the left side, right button if the probe is on the right side). In the assessment task, 50% of the time, the probe will replace the substance image, and in the remaining 50% of the time, it will replace the neutral image. Participants are to complete 200 repeats in the assessment task. There are 10 sets of images, which will be repeated 20 times over the 200 repeats. The time interval between each repeat is 250 milliseconds. In the intervention task, the procedure is like that of the assessment task, with the exception that the probe will always replace the neutral image (100% of the time). This allows for the retraining of biases away from the substance image, and towards that of the neutral image. Participants are to also complete 200 repeats during the intervention task. 

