### 4.1. Statistical Analyses

For data analysis, an intention to treat analytical approach will be used, to include all participants, including those who withdrew and those who are prematurely discharged from the inpatient unit. Microsoft Excel will be used for the computation of the attention bias scores for each participant for each of the assessment task, in accordance to this formula:(∑T_1_/n_1_) − (∑T_0_/n_0_),
where 

T_1_ refers to the time for probes that replaced the neutral stimulusn_1_ refers to number of trials for probes that replaced the neutral stimulusT_0_ refers to the time for probes that replaced the substance stimulusN_0_ refers to number of trials for probes that replaced the substance stimulus

SPSS Version 24.0 (SPSS Inc., Chicago, IL, USA) will be used for the analysis of the quantitative data. Demographic and clinical information data of the subjects in both groups will be summarized using descriptive statistics, including that of means and standard deviations. Chi-square tests will be used to determine if there are differences in the two groups for each of the demographic or clinical information variables. We plan to run ANOVA (analysis of variance) analysis to examine the differences in the outcome measure (attention bias scores/reaction time) across the time points in the actual definitive trial. P-values less than 5% will be considered statistically significant. 

For the qualitative data obtained by means of the perception questionnaire, the data will be coded using NVivo 12, and a thematic analysis approach will be used in the analysis. 

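### The screening text defines the attentional bias score with the opposite sign to the section 4.1 formula, so the positive-bias entry rule is wrong as written

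*Protocol article*

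**What the plan says.** Section 2.2 of the protocol article makes the bias a condition of entry: "participants are required to have baseline attentional biases (i.e., have a positive attentional bias". The Experimental Procedure part of section 3 repeats the rule: "Participants who are screened positive (i.e., having a positive baseline biases) will be eligible to be recruited into the pilot randomized trial". No cut-off other than a positive value is given.

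The score is defined in two places.

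- **Screening for Eligibility (section 3).** The score comes from subtracting the time taken to "respond to probes that replace the neutral image from the reaction time to the probe that replaced the substance image".
- **Statistical Analyses (section 4.1).** The score is (∑T1/n1) − (∑T0/n0), where T1 belongs to probes replacing the neutral image and T0 to probes replacing the substance image. The formula serves the "computation of the attention bias scores for each participant for each of the assessment task".

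Two other passages fix the intended direction. The Introduction describes "attention biases (preferential allocation of attention to substance-related cues". Details of Intervention Tools explains why the training probe always replaces the neutral image: "This allows for the retraining of biases away from the substance image, and towards that of the neutral image".

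**The concern.** Subtracting A from B gives B − A. The screening sentence therefore yields substance time minus neutral time, and section 4.1 yields neutral time minus substance time. A person whose attention is already on the substance image responds faster when the probe appears there. That person scores above zero under section 4.1 and below zero under the screening sentence.

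The bias criterion is settled by the sign of this score. Scored as the screening paragraph is printed, the trial would randomise people who are slower to substance probes, that is, whose attention is directed away from substance images. It would dismiss those with the bias that the training is designed to reduce. The pilot exists to test the processes of the definitive trial, so an uncorrected rule could be carried forward.

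**Working it through.** **Inputs**

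- RT_sub: mean response time when the probe replaces the substance image.
- RT_neu: mean response time when the probe replaces the neutral image.
- Entry rule (section 2.2 and Experimental Procedure): score positive, read here as > 0.
- Share expected to qualify (section 2.4): "approximately 50% of these participants will have baseline biases", of 60 screened.

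The screening sentence does not mention means. I assume that it averages over trials as section 4.1 does.

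**The two definitions**

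- Screening paragraph: S_screen = RT_sub − RT_neu
- Section 4.1: S_4.1 = RT_neu − RT_sub
- Hence S_screen = −S_4.1 for any reaction times.

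**Illustration.** The article gives no reaction times, so 500 and 520 ms are assumptions.

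| Participant | RT_neu | RT_sub | S_4.1 | S_screen | Entry by 4.1 | Entry by screening sentence |
|---|---|---|---|---|---|---|
| Toward substance | 520 | 500 | 520 − 500 = +20 | 500 − 520 = −20 | yes | no |
| Away from substance | 500 | 520 | 500 − 520 = −20 | 520 − 500 = +20 | no | yes |

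The result does not depend on these values. Apart from an exact tie, the two rules never agree on anyone.

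**Which text is out of line.** The Introduction's concept (attention goes to substance cues) implies RT_sub < RT_neu, so S_4.1 > 0. Training away from the substance image presupposes the same direction. Section 4.1 fits both passages and the screening sentence fits neither.

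**Would the recruitment count show a reversal?** The plan's own figure reproduces: 60 × 0.50 = 30 eligible. Under the reversed rule, 60 − 30 = 30 pass. The Introduction also reports that 8 of 17 opioid-dependent participants in the earlier feasibility study had no baseline bias, which leaves 17 − 8 = 9 with bias. If no bias means a score below zero (an assumption):

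- section 4.1 rule: 60 × 9/17 = 31.8, about 32 pass;
- reversed rule: 60 × 8/17 = 28.2, about 28 pass.

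On either basis the count recruited is similar, and that count is the main outcome in section 4.

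**The case against.** The strongest defence is that the screening sentence is a slip of wording and that section 4.1 governs in practice. Section 4.1 applies its formula to each assessment task, and the screening paragraph itself calls the screening test an assessment task. A sentence of the form 'subtract A from B' is easily inverted in writing, and the intended direction can be recovered from the Introduction and the description of the training. This stands as far as it goes: it makes the harm conditional on which text is coded. It does not remove the error. The screening paragraph is where the eligibility score is described, it gives the opposite instruction to section 4.1, and nothing in the article says that a negative screening score counts as bias.

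A reader might infer more than the article supports:

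- **That the trial will enrol the wrong people.** The coded sign in the app and the spreadsheet is not visible, so this is the consequence of following the printed sentence, not an established fact.
- **That eligibility depends on this sign alone.** Section 2.2 also sets conditions on age, diagnosis, primary substance, English literacy and completed detoxification. The sign settles only the bias criterion.
- **That later changes in score would be read in the wrong direction.** Later assessments use the single section 4.1 formula, so a change keeps its meaning whatever the sign at entry. Section 4.1 also places the ANOVA of these scores in the definitive trial.
- **That n1 and n0 must be restricted to correct responses.** This does not follow from unanswered trials being passed over, and such detail can be left to the full protocol or analysis plan.

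**Conclusion.** Wrong as written. This is a contradiction between two printed definitions, not a matter of missing detail or of a figure that fails to reproduce.

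If screening is scored by the printed sentence, all participants with a non-zero score change status on the bias criterion. At the plan's own 50%, the roughly 30 who should enter and the roughly 30 who should be dismissed change places. If screening is scored by section 4.1, enrolment is right and only the written rule is wrong.

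The conclusion rests on reading a positive bias as a score above zero, and on the usual logic of the task that attention to a location speeds the response there. The statement that the recruitment count would probably not reveal a reversal rests on the share with bias being near one half.

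**What to change.** Replace the last sentence of the Screening for Eligibility paragraph with the section 4.1 formula: mean response time to probes replacing the neutral image minus mean response time to probes replacing the substance image, with a positive value meaning bias toward substance. State there that the same formula and sign apply to eligibility and to every later assessment.

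Before the first screening, check the sign coded in the app and in the Excel sheet. Scoring one made-up record with faster responses to substance probes is enough: it should come out positive and eligible.

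The cost is one sentence in the protocol and one check of the scoring. Sample size, procedures and analysis are unaffected.
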